### **2.1 OCTOPUS INTERVENTION DEVELOPMENT**

The first draft of the OCTOPuS intervention has been developed by refining the service currently used in Bournemouth. This has involved compiling the constituent components in the context of cardiac patients. This has been overseen by an intervention development steering group (IDSG), comprising trial investigators, staff from Bournemouth who have

delivered the intervention there, and an anaesthetist. Further input has been obtained from the trial oversight committees, the in-patient diabetes team in Southampton and people with diabetes and experience of cardiac surgery drawn from the study PPI advisory group and local branch of Diabetes UK.

### **2.1.1 Rapid Literature Review**

This has built on current recommendations from the Joint British Diabetes Societies (3), and ensures that all potential elements of the intervention are considered. The literature review comprised two parts; the first review was designed to identify factors that predict poor surgical outcomes in people with diabetes. The purpose of this review was to ensure that the OCTOPuS intervention did not ignore other important risk factors beyond glucose management. The second review was to identify studies that reported pre-surgical admission interventions.

### **2.1.2 Qualitative Data Collection**

Clinicians from cardiothoracic and diabetes disciplines from Bournemouth and Southampton have examined the Bournemouth intervention and findings from the systematic review to discuss the key components of the prototype intervention.

A survey has been developed and distributed to determine current practice for management of people with diabetes in cardiac surgery centres. This will help inform how the OCTOPuS intervention and trial will fit into current clinical practice.

### **2.1.3 Intervention Manualisation**

The learning from the two previous work packages has been synthesised into a first draft of an intervention manual. This will be given to a purposive sample of people with diabetes (sampled to capture diversity in terms of age, occupation, socio-economic status). In addition, discussion regarding the intervention with members of the multidisciplinary cardiothoracic surgery team as well as primary care and specialist diabetes healthcare professionals will take place in order to gain a broad range of key stakeholder views.

This manual will be reviewed and adapted in an iterative process after discussion with our PPI steering group and with clinicians from Southampton, Bournemouth and members of the Trial Steering Committee.

The first draft of the manual includes the review, assessment and management of the following:

- Glucose management (lifestyle and diabetes medication)
- Lipid management
- Hypertension management
- Weight management
  - Diet
  - Exercise
- Smoking cessation
- Support from relative and friends
- Co-ordination of care

### **2.1.4 Training Package Development**

In parallel to developing the OCTOPuS manual, a training package will be developed for OCTOPuS to allow its dissemination across all trial sites. This training package will be an output of the study should the OCTOPuS intervention be shown to be effective.

The same IDSG will oversee the development of the training package, receiving feedback from the OCTOPuS practitioners who are delivering the intervention.

### **2.1.5 Progression rules for moving to main trial**

If a manualised intervention and associated training package cannot be provided, which is acceptable to patients, it will be impossible to deliver the main study. The TSC will review a report of stage 1 from the Trial Management Group, and make a recommendation to stop or proceed.

## **3 STUDY DESIGN**

A single centre, feasibility study to develop an outpatient manualised intervention and associated training package, which is acceptable to people with sub-optimally controlled type 1 or type 2 diabetes undergoing elective cardiothoracic surgery and health professionals.

### **3.1 PRIMARY ENDPOINT**

To produce a manualised intervention and associated training package, which is acceptable to patients and their healthcare professionals that can be used in a multicentre randomised controlled trial involving at least 8 cardiothoracic centres across the UK.

### **3.2 SECONDARY ENDPOINTS**

The following data will be collected on paper CRF pre and post intervention to allow us to report descriptive data about those who have received the intervention:

- Height
- Weight
- Waist circumference
- Sex
- Age
- Diabetes type and duration
- HbA1c
- Smoking status
- Blood pressure
- Blood glucose
- Current medication
- Components of intervention used
- Time from surgery to actual discharge from hospital
- Operations cancelled for sub-optimal glycaemic control

Participants will also be asked to keep a food diary and monitor their blood glucose 4 times per day in the 3 days prior to each phone call to aid discussion about future diabetes management and during interview. These data will not be recorded for trial purposes.

### 3.3 DEFINITION OF END OF STUDY

The end of trial is defined as the date after the last patient has their last interview where all data required to answer the research question are captured.

## 4 SELECTION AND ENROLMENT OF PARTICIPANTS

### 4.1 CONSENT

Consent to enter the study must be sought from each participant only after a full explanation has been given, an information leaflet offered and time allowed for consideration. Signed participant consent should be obtained. The right of the participant to refuse to participate without giving reasons must be respected. After the participant has entered the study the clinician remains free to give alternative treatment to that specified in the protocol at any stage if he/she feels it is in the participant's best interest, but the reasons for doing so should be recorded. In these cases the participants remain within the study for the purposes of follow-up and data analysis. All participants are free to withdraw at any time from the protocol treatment without giving reasons and without prejudicing further treatment.

A traditional approach to seeking consent to take part in the research at the outpatient appointment, and giving patients at least 24 hours to consider the trial and discuss with their social support before making a decision and then returning for their first OCTOPuS consultation presents a challenge. First, it adds a visit to a potentially distant hospital, and second it does not reflect how this intervention would be used should it be rolled out into practice as we would expect the OCTOPuS consultation to usually take place on the same day as the cardiothoracic outpatient appointment. This is necessary to maximise any opportunity to improve diabetes management prior to surgery.

Therefore the study will adopt an approach of informing patients about the study similar to that used by Foss et al (12), who demonstrated that patients receiving telephone based counselling about a trial showed similar levels of comprehension to those being counselled face-to-face. See section 5.1 below for screening and consent procedures.

Upon completion of the informed consent form, a copy will be given to the patient, a copy stored in the patient's medical notes, a copy sent to the SCTU and the original filed in the Investigator Site File. The SCTU copy should be emailed to [[contact]](mailto:[contact]) using a secure nhs.net email address to allow for central monitoring.

### 4.2 INCLUSION CRITERIA

- Adults (aged 18-75 yrs) with sub-optimally controlled type 1 or type 2 diabetes. Sub-optimal control is defined as an  $HbA_{1c} > 53$  mmol/mol using a near patient test at the cardiothoracic outpatients appointment where the decision to proceed to surgery is made.
- Awaiting elective cardiac surgery, where it is anticipated the delay before surgery will be at least 3 months.
- Ability to give informed consent.
- Ability to interact with the study documentation and processes.

### 4.3 EXCLUSION CRITERIA

- Malignancy
- Pregnancy
- Previous cardiac surgery

- Known Haemoglobinopathies
- Other illnesses or conditions that would preclude engagement with the OCTOPuS intervention

#### **4.4 SCREENING FAILURES**

Screen failures will be recorded on the 'patient screening log'. This is completed for all patients who have been considered for the study and is faxed or emailed monthly to the OCTOPuS Trial Team on [name] or [[contact]](mailto:[contact])

#### **4.5 REGISTRATION/RANDOMISATION PROCEDURES**

After consent, participants will be given a sequential trial ID from a provided list. A registration form will be sent to Southampton CTU to centrally document study registrations.

#### **4.6 CONTRACEPTION**

There are no study-specific requirements for the use of contraception.

### **5 STUDY OBSERVATIONS AND PROCEDURES**

#### **5.1 SCREENING PROCEDURES**

Outpatient appointment lists will be scrutinised by research nurses a month ahead of appointments, to identify patients who may meet the study eligibility criteria. For patients who appear eligible for the OCTOPuS study, an information sheet explaining the trial will be sent. Around two weeks before the outpatient appointment a member of the site trial team will telephone the prospective participant to discuss the study, thus allowing sufficient time for reflection and discussion before the outpatient appointment. The information sheet will also include contact details to opt out if the patient does not want to be contacted about the trial. This will allow patients who are eligible for the study at the outpatient appointment to provide consent, and receive their first OCTOPuS consultation, on the same day.

At the outpatient appointment where a decision to proceed to surgery is made, the treating surgeon will remind eligible patients about the trial. If the patient wishes to take part, a more detailed interview with a research nurse will follow, where the study can be discussed in depth according to the needs of the patient, and final exclusion criteria checked (e.g. pregnancy status) and written consent given.

#### **5.2 STUDY PROCEDURES**

Patients will have an initial consultation with an OCTOPuS trained health professional (OCTOPuS Practitioner), who may be a nurse, pharmacist, or other appropriately trained person. In this consultation the patient's diabetes management will be discussed, as well as the likely benefits that improved glycaemic control will provide in the run up to surgery. The practitioner and patient will agree a number of actions, tailored to the individual needs and ability. These are likely to include:

- A graded exercise regimen. This may be completely self-delivered, or alternatively by joining a local appropriate exercise scheme – such as a 'health walk'. There is a general consensus among the cardiothoracic community that limited exercise can be

allowed prior to surgery. This needs to be individualised for each patient, and should not provoke symptoms of angina or breathlessness. The usual format of exercise suggested is walking on the flat, for short, frequent, episodes.

- Dietary advice, possibly supplemented by a consultation with a dietitian
- Medication review, which may lead to the introduction of insulin for people with type 2 diabetes.
- Specific advice about managing expectations, understanding facilitators to achieve change and overcoming barriers to improve medical and psychosocial outcomes

Patients will receive regular review with the OCTOPuS practitioner, probably by telephone, at least once a fortnight. This will be an opportunity to offer encouragement and support, and address any issues which have arisen for the patient.

Where necessary the OCTOPuS practitioner will liaise with local services, e.g. the patient's GP or a dietitian, to facilitate delivery.

### **5.3 FOLLOW UP**

Patients will be interviewed within 6 weeks of receiving their surgery.  
Follow up will be as per local practice.

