|-----------------------------------|-------------------------------------------------------------------------------------------------------------------------------------------------------------------------------------------------------------------------------------------------------------------------------------------------------------------------------------------------------------------------------------------------------------------------------------------------------------------------------------------------------------------------------------------------------------------------------------------------------------------------|
| Secondary Study Endpoints: | Pilot data on: 
 
• Basic demographics of who the intervention is delivered to
 
• Actual time from surgery to actual discharge from hospital
 
• Change in weight between randomisation and surgery
 
• HbA1c immediately preoperative.
 
• Change in HbA1c between baseline and immediately preoperative
 
• Change in blood glucose between baseline and immediately preoperative
 
• Operations cancelled for sub-optimal glycaemic control
 
• Which components of the intervention are used
 
 |
| Total Number of Sites:     | 1                                                                                                                                                                                                                                                                                                                                                                                                                                                                                                                                                                                                                       |

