| Physical Exam (incl height, weight and waist circumference)                                                       |               | X                    |                     |                     |                     |                     |                      |                                   | X       |           |
| Vital Signs (incl. BP)                                                                                            |               | X                    |                     |                     |                     |                     |                      |                                   | X       |           |
| Biochemistry (incl HbA 1c , blood glucose and renal function)                                          |               | X                    |                     |                     |                     |                     |                      |                                   | X       |           |
| Intervention                                                                                                      |               | X                    |                     |                     |                     |                     |                      |                                   |         |           |
| Intervention support phone call a (incl. review of diary card and components of intervention utilised) |               |                      | X                   | X                   | X                   | X                   | X                    | X                                 |         |           |
| Surgery                                                                                                           |               |                      |                     |                     |                     |                     |                      |                                   | X       |           |
| Adverse Events                                                                                                    |               | X                    | X                   | X                   | X                   | X                   | X                    | X                                 | X       | X         |

|                       |  |   |  |  |  |  |  |  |  |                |
|-----------------------|--|---|--|--|--|--|--|--|--|----------------|
| Qualitative Interview |  | X |  |  |  |  |  |  |  | X b |

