| Time to discharge     |  |   |  |  |  |  |  |  |  | X              |
| Surgery details       |  |   |  |  |  |  |  |  |  | X              |

a further support calls may be needed at fortnightly intervals if the surgery is delayed beyond 12 weeks from listing. These phone consultations will not produce data to be captured, but will prompt phone discussion regarding adherence to the intervention and/or during interviews.

b interviews will be conducted within 6 weeks of surgery.

**NB:** The Participant/legal representative is free to withdraw consent at any time without providing a reason. When withdrawn, the participant will continue to receive standard clinical care. Follow up data will continue to be collected unless the participant/legal representative has specifically stated that they do not want this to happen.

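### Participants who start the intervention but never have surgery have no time point for the closing interview or the second HbA1c

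*Protocol*

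**What the plan says.** Section 5.3 of the protocol states: "Patients will be interviewed within 6 weeks of receiving their surgery". Footnote b to the schedule of observations repeats this ("interviews will be conducted within 6 weeks of surgery"). The schedule also marks a qualitative interview at baseline, but that one takes place before the participant has experienced the intervention.

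The physical examination (including weight and waist) and biochemistry (HbA1c, "blood glucose and renal function") are marked at screening and baseline and in the Surgery column, and nowhere else. The synopsis endpoints match: "Change in HbA 1c between baseline and immediately preoperative", the same for blood glucose, and weight change up to surgery.

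Section 3.2 words the timing differently: "The following data will be collected on paper CRF pre and post intervention". The schedule contains no post-intervention visit that is separate from surgery.

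Non-surgery is foreseen. The synopsis and section 3.2 both list "Operations cancelled for sub-optimal glycaemic control" as an outcome. For delayed surgery, footnote a says that "further support calls may be needed at fortnightly intervals if the surgery is delayed beyond 12 weeks from listing", and adds: "These phone consultations will not produce data to be captured".

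**The concern.** The primary endpoint in section 3.1 is a manual and training package acceptable to patients and professionals, and section 2.1.5 makes acceptability to patients the condition for going on to the main trial. Patients' experience of the whole intervention is gathered at the closing interview. Someone who received the intervention and was then taken off the surgical list is never due for that interview, and may be among those with most to say about why it did not work.

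For HbA1c the problem is more specific. When an operation is cancelled because glucose control is still poor, the reason the value is missing is linked to the value itself. A mean change among operated participants would then tend to look better than the mean among all who started.

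The protocol's own figures make such cancellations plausible. Section 1.2 cites UK guidance recommending delay above 69 mmol/mol, while section 1.1 reports that the Bournemouth service reached 74 mmol/mol on admission after its intervention.

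**Working it through.** **Is there any other time point?** Taking the candidate passages in turn:

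- Section 5.3 and footnote b: the interview is counted from surgery only.
- Schedule: post-baseline biochemistry and physical examination appear in the Surgery column only.
- Section 5.6: participants who withdraw from treatment stay in follow-up on the trial schedule, which is the same surgery-based schedule.
- Section 3.2: the wording does not require an operation, but no visit implements it.
- Section 3.3: the study ends after the last patient's last interview, yet no closing interview ever falls due for an unoperated participant.
- Appendix 1, written for the main trial, recognises patients who finish the intervention and then have surgery cancelled or postponed. The pilot schedule has no counterpart.

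So no passage supplies a time point for a participant who is never operated on.

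**Number of starters.** Section 7.1 gives about 20, from up to 4 cycles of 4-6 people. 4 × 5 = 20 reproduces this, with a range of 4 × 4 = 16 to 4 × 6 = 24. The synopsis gives 20-30, and its upper end exceeds 24. The illustration uses 20; for HbA1c only the unoperated fraction matters.

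**Size for HbA1c (assumptions, not trial data).** Section 1.1 gives 85 − 74 = 11 mmol/mol for the Bournemouth service, taken here as the mean reduction in operated participants. The documents state no rate of non-surgery, so k unoperated participants out of 20 is varied, with mean reduction c among them.

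All-starter reduction = [(20 − k) × 11 + k × c] / 20

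| k | c | All-starter reduction | Operated-only figure minus all-starter figure |
|---|---|---|---|
| 1 | 0 | 19 × 11 / 20 = 10.45 | +0.55 |
| 2 | 0 | 18 × 11 / 20 = 9.9 | +1.1 |
| 4 | 0 | 16 × 11 / 20 = 8.8 | +2.2 |
| 4 | 11 | 11.0 | 0 |
| 4 | 15 | (176 + 60) / 20 = 11.8 | −0.8 |

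The operated-only figure is too high if unoperated participants do not improve, right if they improve equally, and too low if they improve more.

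**Acceptability.** The protocol plans no acceptance proportion, so this only shows what is left undetermined. Suppose 4 of 20 are not interviewed and 13 of the other 16 (81%) find the intervention acceptable. The all-starter figure then lies between 13/20 = 65% and 17/20 = 85%, on either side of the observed value. Within a cycle of 4-6 people, one lost interview removes 1/6 to 1/4 (17% to 25%) of the closing patient feedback that informs the next refinement.

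**The case against.** A reader might infer that every assessment after baseline depends on surgery, that deferred participants are lost too, and that both acceptability and HbA1c are biased towards success. The documents do not support this.

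- The intervention components used and adverse events are collected at the week 2 to 12 calls. Section 7.2 also includes interviews with healthcare professionals and sets no surgery trigger for them.
- Deferred participants stay in the study with further calls and reach the surgery assessments later. Since section 1.2 describes delay as the UK response to a high HbA1c, some glycaemic cancellations may prove to be deferrals, and the affected group may be small.
- A direction of bias is plausible only for HbA1c after a glycaemic cancellation. Nothing links non-surgery for other reasons to HbA1c, or non-surgery of any kind to disliking the intervention.
- Glycaemic cancellations are not hidden, because they are counted as an outcome. An HbA1c taken before a late cancellation might exist, though nothing requires it to be recorded.
- HbA1c is descriptive here. The HbA1c cut-offs in Appendix 1 refer to 50 intervention and 50 control patients, so they belong to the main trial. Acceptability is judged by thematic analysis and by the Trial Steering Committee on a report, not against a proportion.

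All of this stands, and it limits the consequence. One could add that denominators and missing values commonly belong in a statistical analysis plan, which is also fair. But an analysis plan cannot recover an interview that was never scheduled: the gap is in data collection, and that is set in the protocol.

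Interviewing after surgery is itself defensible, since section 7.2 also asks about follow-up care.

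**Conclusion.** The point holds in a limited form. The protocol provides no closing interview and no post-baseline HbA1c, glucose, weight or waist measurement for a participant who starts the intervention and never has surgery, a situation its own outcome list anticipates. Followed as written, it would take closing patient feedback and HbA1c change from operated participants only.

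For glycaemic cancellations the likely effect is an overstated HbA1c reduction, by about 0.6 to 2.2 mmol/mol if 1 to 4 of 20 are unoperated with no change against 11 mmol/mol in the rest. Those counts and the zero change are assumptions. For other reasons for non-surgery, and for acceptability, the direction is unknown. The study has no numerical threshold that this would breach. The main loss is that the primary question, acceptability to patients, would not cover everyone who received the intervention.

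**What to change.** In section 5.3 and footnote b, keep the interview within 6 weeks of surgery and add a fallback: if the operation is cancelled without a new date, or the participant leaves the surgical list, the interview takes place within 6 weeks of that decision; participants still waiting when the study is due to close are interviewed then.

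Do not use a fixed cap counted from the first consultation, such as 12 + 6 = 18 weeks. Section 4.2 requires an expected wait of at least 3 months, so a cap would pull forward the interviews of people still waiting and still receiving support calls.

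For unoperated participants, record the latest available HbA1c, glucose and weight with their dates. Reconcile the timing in section 3.2 with the synopsis endpoints and the schedule. Report interview and HbA1c results alongside the number of all starters, showing operated and unoperated participants separately.

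The cost is a few extra telephone interviews, a small addition to the CRF, and HbA1c values at less uniform times in the unoperated group. The change concerns data collection only and leaves clinical management untouched.
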